## Abstract

**Background:**

Despite the known adverse effects of maternal overt hypothyroidism on the neurocognitive development of children, there is uncertainty regarding the impact of gestational thyroid dysfunction or autoimmune thyroiditis on infant/child neurological development. This study aims to evaluate the impact of levothyroxine (LT4) treatment on the psychomotor developmental status of three-year-old children born to mothers with mild thyroid impairment (subclinical hypothyroidismwith/without autoimmune thyroiditis).

**Methods/Design:**

This is a follow-up study of the Tehran Thyroid and Pregnancy Study, a randomized trial in which subclinical hypothyroid pregnant women were assigned to an intervention group (treated with levothyroxine) or a control group (received no treatment). The primary outcome for the purpose of the present study is the developmental status of the children, aged three years, in five domains (communication, gross motor, fine motor, problem-solving, and social–personal domains) using the Ages and Stages Questionnaire (ASQ).

**Discussion:**

The study is designed to assess the developmental status of children born to mothers with mild thyroid impairment (subclinical hypothyroidism with/without autoimmune thyroiditis). This study is one of the limited studies available in this field and has the potential to facilitate much-needed information for related public health policies.

**Trial registration:**

Iranian Registry of Clinical Trials, IRCT2017090314849N5. Registered on 11 September 2017. Iranian Registry of Clinical Trials, IRCT2017090414849N6. Registered on 14 October 2017.

**Electronic supplementary material:**

The online version of this article (10.1186/s13063-018-3130-5) contains supplementary material, which is available to authorized users.

## Background

Several studies revealed the distinguishable role of maternal thyroid hormones on all stages of brain cell development [1, 2]. In the first trimester of pregnancy, a time when the embryo’s thyroid is still developing, fetal thyroid hormones are completely dependent on the mother as a source. However, after this stage, the mother and fetus both contribute to this need. Studies revealed the presence of specific nuclear receptors and thyroid hormones in the fetal brain at the eight week of gestation and free T4 in the coelomic and amniotic fluids, underling the role of thyroid hormones in early fetal brain development [3].

Both overt hypothyroidism and hyperthyroidism are well-known modifiable risk factors for various fetomaternal and child outcomes [4, 5]. Data regarding the adverse pregnancy and child outcomes of subclinical forms of thyroid dysfunction or thyroid autoimunity are inconclusive and treatment benefits in such women are unclear. Despite observational studies reporting significant association between mild gestational thyroid dysfunctions and several pregnancy complications or neurocognitive impairment in the offspring [6–14], treatment of subclinical hypothyroidism (SCH) or hypothyroxenemia have not improved pregnancy outcomes or even cognitive functions in their children in limited randomized clinical trials (RCT) carried out among pregnant women [15–17]. The results of studies on the effects of maternal autoimmune thyroid disorders on cognitive development in children also differ. Pop et al. in 1995 reported that the neurodevelopmental scores of children of TPOAb-positive (TPOAb^+^) mothers were significantly worse than those with TPOAb-negative (TPOAb^−^) mothers [18]; in contrast, Williams et al. [19] demonstrated no evidence of an association between maternal TPOAb and TSH levels and neurodevelopmental outcome. Li et al. [11] showed that the intellectual and motor development of children aged 25–30 months is associated with abnormalities of maternal thyroid at 16–20 weeks’ gestation; maternal SCH or euthyroidism with elevated TPOAb titers were found to be predictors of lower motor and intellectual development. Ghassabian et al. [20] showed that higher titers of TPOAbs during pregnancy were associated with an increase in children’s risk of attention deficit/hyperactivity; however, this adverse effect was not observed in the Controlled Antenatal Thyroid Screening (CATS) study [21, 22] that investigated treatment for SCH on childhood cognition and found no differences in IQ at the ages of three years and 9.5 years between children of treated and untreated SCH mothers. In addition, studies by Casey et al. (2017) and Lazarus et al. (2012) showed maternal treatment for SCH did not result in improved cognitive function in children [15, 17].

Hence, considering the fact that the effect of treatment on the development status of offspring is not clear, in this follow-up clinical trial study, we aim to evaluate the impact of levothyroxine (LT4) treatment on the psychomotor developmental status of three-year-old children born to mothers with mild thyroid impairment (SCH with/without autoimmune thyroiditis).

## Methods

### Overall trial design

This is the follow-up study from The Tehran Thyroid and Pregnancy Study [23], a two-phase population-based RCT carried out on pregnant women referring to prenatal clinics of Shahid Beheshti University of Medical Sciences. In brief, in the first phase of that study, using a cluster-sampling method, first-trimester pregnant women were screened for thyroid disorders; in the second phase of the study, those with SCH (both TPOAb-positive and -negative) were randomly assigned to be treated with levothyroxine (intervention) or to receive no treatment. The details of the original study have been published before [23].

The Tehran Thyroid and Pregnancy Study was conducted from September 2013 through February 2016. The first phase of this study was a population-based cross-sectional study in which 1746 pregnant women attending the prenatal clinics of Shahid Beheshti University of Medical Sciences were screened for thyroid dysfunction. Overnight blood samples were collected at the first prenatal visit and second (20–24 weeks of gestation) and third (30–34 weeks of gestation) trimesters to measure serum levels of TSH, thyroxine (T4), resin T-uptake (RTU), and TPOAb. Table 1 shows the classification of mothers according to the level of TSH, FT4I, and TPOAb.

**Table 1 Tab1:** Classification of mothers according to the level of TSH, FT4I, and TPOAb

Classification	TSH (mIU/L)	FT4I	TPOAb (IU/mL)
Euthyroid	0.1–2.5	1–4.5	< 50
Overt hyperthyroidism	< 0.1	> 4.5	–
SCH	< 0.1	1–4.5	–
Overt hypothyroidism	> 10	-	–
Overt hypothyroidism	> 2.5	< 1	–
SCH TPOAb^−^	2.5–10	1–4.5	< 50
SCH TPOAb^+^	2.5–10	1–4.5	> 50

*TPOAb* thyroid peroxidase antibodies, *SCH* subclinical hypothyroidism

At the first prenatal visit, participants were asked to collect three casual morning urine samples (5–10 mL) every other day.

After excluding those with twin pregnancies and those with overt thyroid dysfunction or SCH (*n* = 127), euthyroid women and those with other types of thyroid dysfunction (*n* = 1619) were invited for the second phase of the study. Two RCTs, one of TPOAb^+^ cases (*n* = 131) [24] and the other of SCH–TPOAb^−^ women (*n* = 366) [25], were conducted in the second phase of the study; the remaining 1028 euthyroid TPOAb^−^ women served as controls and were followed until delivery (Fig. 1).

**Fig. 1 Fig1:**
[figure not shown]
Study *flow chart*

SCH–TPOAb^−^ women and TPOAb^+^ cases were randomly assigned into two groups (using a computer-generated list) to achieve balance across treatment groups, according to permuted blocks of four; the LT4 treatment group was treated with LT4 and the placebo group went without treatment. Women in the LT4 treatment group received LT4: a morning dose of 1 μg/kg/day, a dose maintained throughout the pregnancy. In brief, for the purpose of the present study, we have five groups including two cases (TPOAb^+^ treated with LT4 and SCH–TPOAb^−^ treated with LT4) and three controls (TPOAb^+^ not treated with LT4, SCH–TPOAb^−^ not treated with LT4, and euthyroid TPOAb^−^ women).

### Neurodevelopmental study of offsprings

Both groups of children (aged three years) born to mothers with SCH and/or autoimmune thyroid disease will be invited to participate. In the present study, parents will complete the Ages and Stages Questionnaire to assess the children’s developmental status. The children of those euthyroid TPOAb^−^ women will also be invited to be participate in this follow-up study and serve as controls (Fig. 1).

Participants will be contacted by phone; the aim and purpose of the present study will be explained in detail. An appointment will be arranged for those participants who wish to complete the development assessment. A trained examiner will explain the instructions for completing the questionnaire. All assessments will be performed by one examiner only to maximize reliability. A randomly selected 5% of the completed assessments will be retested in two weeks and double-scored to ensure the reliability; the scores are calculated and a report is generated for the participants to be taken to their parents. If participants need to be given more information about the results or have any questions, they can contact the examiner directly.

In the present study, the ASQ, a parent-report questionnaire, was chosen because it has been proven to be a valid and/or reliable screening test for Iranian infants and children [26]. The ASQ questionnaire assesses the developmental status of children aged 4–60 months (in 19 age groups) in five developmental domains including communication, gross motor skills, fine motor skills, problem-solving, and social–personal domains. It includes six open-ended questions that assess the parents’ concerns such as visual and auditory problems. Each age-specific domain includes six items, scores are in the range of 0–60 in each subscale, and the total score is in the range of 0–300 [27]. The scoring system is based on a 10–5–0 scoring scale (10 points for every “yes,” 5 points for every “sometimes,” and 0 points for every “not yet” answer to the questions). The sum of scores is then compared with a list of age-specific cut-off points standardized for Iranian children [26, 28].

ASQ validity has been examined across different cultures and communities across the world [29–32] and has excellent psychometric properties (test–retest reliability of 92%, sensitivity of 87.4%, and specificity of 95.7%) [26, 29, 31–33]. The inter-rater reliability values obtained were 0.88, 0.91, 0.88, 0.89, and 0.86 for the communication, gross motor skills, fine motor skills, problem-solving, and social–personal domains, respectively, and 0.93 totally [26]. It had the ability to precisely determine developmental disorders in > 96% of children [34].

The study protocol has been designed and reported in line with SPIRIT guidelines, with an attached SPIRIT flow diagram (Fig. 2) and checklist (Additional file 1) [35].

**Fig. 2 Fig2:**
[figure not shown]
Summary of study events schedule. TPOAb thyroid peroxidase antibodies, TSH thyroid stimulating hormone, LT4 levothyroxine, ASQ Ages and Stages Questionnaires

### Ethics approval

Written informed consent will be obtained from all participants by the examiner. It will be emphasized that participation in the study is voluntary and they were free to withdraw from the study at any time.

Both original and current studies have been been approved by the Medical Ethics Committee of the Research Institute for Endocrine Sciences of Shahid Beheshti University of Medical Sciences and received two separate codes for studies among TPOAb^+^ women and among SCH TPOAb^−^ ones (approval code numbers for original study: IR.SBMU.ENDOCRINE.REC.1395.297 and IR.SBMU.RIES.REC.1394.48, approval code numbers for current study IR.SBMU.ENDOCRINE.REC.1395.299 and IR.SBMU.ENDOCRINE.REC.1395.300). They also were registered in the Iranian Randomized Clinical Trials (IRCT) Registry (trial codes for original study: IRCT2013100114849N1, IRCT2013112014849N2, and IRCT2013121214849N3; trial codes for current study: IRCT2017090414849N6 and IRCT2017090314849N5).

### Power calculation and sample size justification

The purpose of this study will be multiple comparisons of five groups: three groups of controls: no intervention TPOAb^+^, no intervention TPOAb^−^, and healthy; as well as two cases: intervention TOPAb^+^ and TPOAb^−^. We will consider five primary outcomes: communication; gross motor skills; fine motor skills; problem-solving; and social–personal aspects.

Post-hoc power calculation was done to detect samples needed. It has been shown that, with power of 80% and type one error of 5%, nearly 2356, 590, 263, 149, 96, 67, 50, 39, and 31 participants are required to find the effect sizes 0.1, 0.2, 0.3, 0.4, 0.5, 0.6, 0.7, 0.8, and 0.9 statistically significant. We will consider q = 15% attrition as well which increases sample size by n* = n/1-q. The following formula for comparison of groups is applied:$$ \boldsymbol{n}\boldsymbol{\ge}\left(\mathbf{1}+\sqrt{\boldsymbol{g}-\mathbf{1}}\right)\frac{{\left({\boldsymbol{z}}_{\mathbf{1}-\frac{\boldsymbol{\alpha}}{\mathbf{2}}}+{\boldsymbol{z}}_{\mathbf{1}-\boldsymbol{\beta}}\right)}^{\mathbf{2}}}{{\boldsymbol{d}}^{\mathbf{2}}}+\frac{{\boldsymbol{z}}_{\mathbf{1}-\frac{\boldsymbol{\alpha}}{\mathbf{2}}}^{\mathbf{2}}\sqrt{\boldsymbol{g}-\mathbf{1}}}{\mathbf{2}+\left(\mathbf{1}+\sqrt{\boldsymbol{g}-\mathbf{1}}\right)} $$

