### Statistical analysis

Intention to treat (ITT) analysis will be considered to deal with non-compliance and missing outcomes in our RCT.

Dataset accuracy will be checked using histograms and cross-tabulations to identify any outliers and errors. We will also run “Grubbs” test, an ESD (method extreme studentized deviate), to determine whether any values are significant outliers or implausible values > 4 SD from the mean will be considered as outliers and discarded. Descriptive statistics will be presented as means ± SD for normal, medians and IQR for non-normal variables, and categorical variables presented as percent.

Normality assumption will be checked by Kolmogorov–Smirnov and Shapiro–Wilk test; in case of rejection, the Mann–Whitney non-parametric U test will be applied, otherwise independent Student’s t test will be used to find the differences. For categorical variables, chi-squared test and/or Fisher’s exact test in case of a sparse data problem (cell < 5) will be used. Subgroup analysis for important confounding variables will be run, if needed.

The primary analysis for the study is to assess the effect of treatment on the aspects of psychomotor developmental status. Therefore generalized linear models (GLM) will be conducted modeling the variables and checking the causal relationships between the outcome of interests and other covariates such as treatment. Crude and adjusted models for potentially confounding effects will be fitted.

Interaction effect of treatment and some other covariates will be added to the model and a subgroup analysis will be run to check the effect of treatment on the levels of covariates, variables such as parity, socioeconomic status, type of delivery, lactic status, urinary iodine, and so on.

Since our study follows up the second generation of the ancestors whom intake the intervention, the casual relationships could be assessed via transitional models. There is a series of statistical analyses to estimate these relationships; we use transitional models which applied Markov Chains stochastic process and multistate models.

Statistical analysis will be performed using STATA software (version 10; STATA, Inc., College Station, TX, USA) and the latest version of R CRAN, the “msm” package, to analyze multi-state modelling with R; *p* < 0.05 is considered statistically significant.

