The key strength of the present study is assessing the neurodevelopmental status of the offspring of both groups of TPOAb^+^ cases and SCH-TPOAb^−^ women along with euthyroid TPOAb^−^ women, considering their iodine sufficiency status during pregnancy. We are not aware of any other studies that have considered all these components simultaneously. The other strength of this study is the ASQ and the number of characteristics assessed. First,the Persian version of the ASQ has appropriate validity and reliability for screening developmental disorders in Iran [26]. It has also been proven to be a valid and/or reliable screening test, i.e. it has translated and culturally adapted versions in several studies in different populations of children [28]. In a multinational trial involving 18 countries in Asia, Africa, Europe, North America, and South America reported in 2007, the sensitivity and specificity were determined to be 88% and 82.5%, respectively [45, 46]. It also uses simple and straightforward language; simple illustrations are provided for many items adding to their clarity of meaning, which makes it a feasible and easy-to-use test [47]. It is inexpensive [47, 48] and takes about 10 min to administer [47]. Administration does not require specialized training. This series of developmental screening questionnaires includes five developmental domains: gross motor skills; fine motor skills; communication; problem-solving; and personal–social domains. The questionnaires cover 19 age groups in the range of 4–60 months [49].

The main challenge of this study will be the rate of attrition; however, its pilot study received a response rate of > 80%. The other challenge of this study is lack of awareness of other factors that may influence the developmental status of the children, e.g. nutritional inadequacies [50], although the randomized allocation of study participants minimizes this effect.

By conducting this study, we hope to better understand the beneficiary impact of treatment of mild forms of thyroid dysfunctions during pregnancy, considering the influential effect of iodine status. This piece of knowledge has the potential for evidence-based decision-making regarding the universal screening for thyroid dysfunction and/or thyroid autoimmunity.

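### Five primary ASQ domains are tested at p < 0.05 with no control of the overall error, so even a single randomised comparison carries about a 10–23% chance of a false-positive primary finding

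*Protocol article*

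**What the plan says.** All of this is in the protocol article.

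- **Power calculation and sample size justification.** The aim is put as "The purpose of this study will be multiple comparisons of five groups": two treated groups, two untreated groups and a euthyroid group. The endpoints follow: "We will consider five primary outcomes", one for each ASQ domain. The list of sample sizes is derived "with power of 80% and type one error of 5" per cent.
- **Statistical analysis.** The primary analysis is the effect of treatment on the aspects of development, by generalised linear models (GLM), both crude and adjusted. The section also provides for a t test or Mann–Whitney test, chosen after normality tests, and for interaction and subgroup analyses. One threshold closes the section: p < 0.05 "is considered statistically significant".
- **Overall trial design.** Two randomised trials are described, one in TPOAb+ women (131) and one in SCH-TPOAb− women (366). A further 1028 euthyroid women were followed without randomisation. Ethics approval and Trial registration give the follow-up two registration numbers.
- **Discussion, Principal findings.** Of unmeasured influences on child development, the article says "although the randomized allocation of study participants minimizes this effect", without saying which comparisons this covers.

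**The concern.** With five primary outcomes and no rule for combining them, nothing in the article prevents one domain at p < 0.05 from being presented as a positive primary result. The error rate that governs such a claim is the chance that at least one of the tests is falsely significant. The article neither states nor controls that rate. The Discussion ties the results to decisions on universal thyroid screening, so a chance finding in one domain could carry weight.

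A second, separate gap is that the article does not say which group contrasts are confirmatory. Only LT4 versus no treatment within each trial is protected by randomisation. A comparison with euthyroid women, or between TPOAb+ and SCH-TPOAb− women, is observational. As written, both kinds share one list of groups and one threshold.

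**Working it through.** **Step 1. Was alpha adjusted in the sample size?** The article's formula with g = 5 gives √(g−1) = 2. With z(1−α/2) = 1.960 and z(1−β) = 0.842:

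n = 3 × (1.960 + 0.842)² / d² + 1.960² × 2 / 5

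- d = 0.1: 2354.7 + 1.5 = 2356.2 (stated 2356)
- d = 0.2: 588.7 + 1.5 = 590.2 (stated 590)
- d = 0.5: 94.2 + 1.5 = 95.7 (stated 96)

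All nine stated figures reproduce to within one participant. Alpha enters only through 1.960, so the unadjusted 0.05 was used. The factor 1 + √(g−1) = 3 depends on the number of groups, but it multiplies n as an allocation factor. It does not adjust alpha.

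**Step 2. Chance of at least one false-positive domain.** For independent tests this is 1 − 0.95^m.

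- One trial, five domains: 1 − 0.95⁵ = 22.6%
- Both trials, ten tests: 1 − 0.95¹⁰ = 40.1%

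ASQ domains are likely to be correlated, but the article gives no correlation, so a range is assumed. The correlated rows come from a simulation of 200,000 runs with group sizes 183/183 and 65/66 and equal correlation between all domains.

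| Assumed correlation | One trial × 5 domains | Both trials × 5 domains |
|---|---|---|
| 0 | 22.6% | 40.1% |
| 0.3 | 20.8% | 37.4% |
| 0.5 | 18.4% | 33.3% |
| 0.7 | 15.0% | 27.7% |
| 0.9 | 10.2% | 19.4% |

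As a check, the two trials share no participants, so at correlation 0.9 the second column should be 1 − (1 − 0.102)² = 19.4%, which it is. These rates assume one test per domain. They leave out any choice between t test, Mann–Whitney, crude GLM and adjusted GLM.

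**Step 3. What control would do to the stated sample sizes.** Holm's first step for five tests is 0.05 / 5 = 0.01, with z = 2.576. The article's formula then gives:

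- d = 0.2: 3 × (2.576 + 0.842)² / 0.04 + 2.576² × 2 / 5 ≈ 879, against 590
- d = 0.5: ≈ 143, against 96

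Take 590 as the larger group in the 2:1 comparison that the factor 3 implies (590 and 295). The standardised effect at d = 0.2 is 0.2 × √(590 × 295 / 885) = 2.805. Power is Φ(2.805 − 1.960) = 80% at α = 0.05 and Φ(2.805 − 2.576) = 59% at α = 0.01.

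**Step 4. Detectable difference in the actual trials.** With 15% attrition, the formula is (z(1−α/2) + 0.842) × √(1/n₁ + 1/n₂).

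- SCH-TPOAb−, 155.55 per arm: the root is 0.1134. This gives 2.802 × 0.1134 = 0.32 SD at α = 0.05 and 3.417 × 0.1134 = 0.39 SD at α = 0.01.
- TPOAb+, 55.25 and 56.1: the root is 0.1895. This gives 0.53 SD and 0.65 SD.

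**The case against.** **The primary family is narrow.** The Statistical analysis section names the treatment effect as primary, and comparisons with euthyroid women are not treatment effects. This stands. A reader might take the stated purpose of comparing five groups to mean 10 pairs × 5 domains, or 50 primary tests, for which the simulated error is about 46–79%. The article never lists 10 pairs or 50 tests as primary, so that figure should not be used as the size of the problem. The narrow reading reduces the problem but does not remove it, because five tests per trial remain.

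**The 5% is a per-test figure.** This is correct. The article makes no familywise promise, and each single test holds its level. What is missing is control over the set of primary claims.

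**The domains might all have to succeed.** That rule would remove the inflation from the five domains, but the article does not state it.

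**An unseen analysis plan may settle this.** It may. The article itself, however, fixes five primaries, one threshold and a sample size at unadjusted alpha. A later adjustment would not fit its power statement (Step 3).

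**Non-randomised contrasts.** A reader might infer that they cause the error inflation. They do not: confounding is a separate matter, and the inflation remains if they are dropped. A reader might also cite Table 2, where gestational age is 37.9 weeks in untreated SCH-TPOAb− women and 39.4 in euthyroid women (difference 1.5, SE 0.12), as proof of baseline imbalance. That does not work. Gestational age at birth comes after maternal thyroid status and treatment. It also differs within the randomised TPOAb+ pair, 39.3 against 38.4 (difference 0.9, SE √(1.3²/65 + 1.7²/66) = 0.26).

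**The Discussion sentence on randomisation** is fair for the two randomised contrasts, and adjusted models are planned. Its fault is only that its scope is left open.

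**Conclusion.** The point holds in a limited form. Followed as written, the plan gives about a 10–23% chance of at least one false-positive primary domain within a single randomised trial, and about 19–40% over the two trials together. The ranges rest on assumed inter-domain correlations of 0.9 to 0, no true effect in any domain, and one test per domain. The single-trial figure is the more relevant one if each registration is judged alone. In one trial the rate would fall to 5% only if the five domains were perfectly correlated.

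The failure to mark off randomised from observational contrasts is a second, distinct gap in the same text. It bears on confounding and on what may be claimed, not on the error rates above.

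**What to change.** 1. State that the confirmatory comparisons are LT4 versus no treatment within each registered trial.
2. In each trial, test the five domains with Holm's procedure at an overall two-sided 5%: smallest p against 0.01, then 0.0125, 0.0167, 0.025 and 0.05, stopping at the first failure.
3. Name in advance the one GLM-based treatment estimate whose p-value enters Holm. Treat other analyses of the same contrast as sensitivity analyses.
4. Label comparisons with euthyroid women or across the two trials as secondary, observational and confounder-adjusted, with confidence intervals and no confirmatory claim.
5. Report any LT4 effect pooled over the two trials as supportive only. Without its own alpha, a pooled test in five domains would bring the multiplicity back.
6. Limit the Discussion sentence on randomised allocation to the two randomised contrasts.
7. Restate the power statement at the adjusted alpha.

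**Cost.** No new data are needed, but sensitivity is lost. At the strictest Holm step (α = 0.01, 80% power, 15% attrition) the detectable difference rises from about 0.32 to 0.39 SD in SCH-TPOAb− and from about 0.53 to 0.65 SD in the smaller TPOAb+ trial. Holm within each trial still leaves up to 1 − 0.95² = 9.75% over both. That is defensible for two separately registered trials. If one joint claim is intended, the ten tests form one family, the first step is 0.005, and the detectable differences become about 0.41 and 0.69 SD. The choice should be recorded before the outcome data are analysed.

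### The listed sample sizes are shared-control-group sizes for a many-to-one layout, are not labelled, and do not give 80% power for the randomised 1:1 LT4 comparisons

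*Protocol article*

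**What the plan says.** The section on power and sample size (protocol article, Methods) gives the aim as follows: "The purpose of this study will be multiple comparisons of five groups". It names three control groups and two treated groups. For a calculation "with power of 80% and type one error of 5"%, it lists nine sample sizes against nine standardised effects: "nearly 2356, 590, 263, 149, 96, 67, 50, 39, and 31 participants are required to find the effect sizes" from 0.1 to 0.9. It adds "We will consider q = 15% attrition as well which increases sample size" and prints a formula in g, the number of groups. No target effect is chosen, and the listed numbers are called participants without further label.

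The design is described elsewhere. Under Overall trial design, women in each antibody stratum were randomised to LT4 or no treatment "according to permuted blocks of four". Table 2 gives 183 vs 183 (SCH-TPOAb−), 65 vs 66 (TPOAb+) and 1028 euthyroid women. The Statistical analysis section makes the effect of treatment the primary analysis.

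**The concern.** The formula belongs to a different layout from the one that answers the primary question. A reader who wants to know what the two randomised comparisons can detect cannot get it from the list, and goes wrong in a direction that depends on how the unlabelled n is read.

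- **Read as a two-arm total:** 263 inflated for attrition is 263/0.85 = 309.4, so 310. The 366 SCH-TPOAb− women then look ample for d = 0.3. Likewise 96/0.85 = 112.9, so 113, and the 131 TPOAb+ women look ample for d = 0.5. After 15% loss each comparison has about 75% power at those effects.
- **Read per arm:** the list makes the cohort look weaker than it is. Solving the formula for n = 183 gives d = 0.36, whereas 183 vs 183 detects 0.29 before attrition.

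The Discussion hopes that the results will inform decisions on universal screening. The stated sensitivity of the smaller TPOAb+ trial therefore matters.

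**Working it through.** **Inputs.** Two-sided alpha 0.05 (the formula uses z at 1−α/2), power 80%, d in SD units, g = 5, attrition 15%: all from the power section. Group sizes 183/183, 65/66 and 1028: Table 2. Normal approximation throughout.

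**1. Reproducing the list.** (1.960 + 0.842)² = 7.849 and √(g−1) = 2, so the leading term is 3 × 7.849/d². With the last denominator read as a product, 2 × (1 + 2) = 6, the second term is 3.84 × 2/6 = 1.28. For d = 0.1 to 0.9 this gives 2355.9, 589.9, 262.9, 148.4, 95.5, 66.7, 49.3, 38.1 and 30.4. Rounded up, these match all nine stated figures. With the printed plus sign the denominator is 5, the second term is 1.54, and the first three become 2357, 591 and 264. The plus sign therefore looks like a typesetting slip. Setting g to 2, 3, 4 or 6 does not reproduce the list.

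**2. What the list measures.** For a control group of size n and a comparator of size n/k, the variance of the difference in means is (1 + k)/n. Solving for n gives (1 + k)(z + z)²/d², the protocol's leading term with k = √(g−1) = 2. So n is the shared control group, and each of the four other groups has n/2. At d = 0.3 that is 263 + 4 × 132 = 791 women. Check: 263 vs 131.5 gives 80.2% power.

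**3. The same n in a 1:1 comparison, d = 0.3.** Power = Φ(d/√(1/n₁ + 1/n₂) − 1.960).

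| Reading of 263 | n₁ vs n₂ | Power |
|---|---|---|
| total of two arms | 131.5 vs 131.5 | 68% |
| per arm | 263 vs 263 | 93% |

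Across all nine effects the ranges are 68–71% and 93–94%. The 1:1 requirement at d = 0.3 is 2 × 7.849/0.09 + 0.96 = 175.4, so 176 per arm (352 in all).

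**4. What the cohort can detect.** Detectable d = 2.802 × √(1/n₁ + 1/n₂), after 15% loss in every group:

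| Comparison | n after loss | Detectable d (80% power, two-sided 5%) |
|---|---|---|
| SCH-TPOAb−, LT4 vs none | 156 vs 156 | 0.32 |
| TPOAb+, LT4 vs none | 55 vs 56 | 0.53 |
| Euthyroid vs one SCH-TPOAb− arm | 874 vs 156 | 0.24 |
| Euthyroid vs one TPOAb+ arm | 874 vs 55 | 0.39 |

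Power at d = 0.3 is about 75% in SCH-TPOAb− and about 35% in TPOAb+.

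**5. Sensitivity to attrition.** The Discussion reports that "its pilot study received a response rate of > 80"%. At 20% loss, the other end of a plausible range, the randomised comparisons detect 0.33 SD (146 vs 146) and 0.55 SD (52 vs 53).

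**The case against.** Much can be said for the protocol. The nine figures are correct for the formula used. A five-group formula has a basis in the text, because comparing five groups is the stated purpose and there is a large euthyroid reference group. For that comparison the list is usable in part: at d = 0.3 it asks for 263 controls and about 132 in each other group, and after loss 874 and 156 exceed both, although the TPOAb+ arms (about 55) do not. All of this stands, and it is why the euthyroid comparison should keep a calculation. It does not rescue the list for the treatment effect. Nor is the euthyroid layout 2:1: 1028 to 183 is about 5.6:1, and 1028 to 65 about 16:1.

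A reader might infer that the protocol claims 80% power for this trial and that the claim is false, or that the trial is shown to be underpowered. The text supports neither. The 80% is an input to a table of n against d, no target effect is chosen, and no power is claimed for 183/183 or 65/66. Read per arm, the list is conservative.

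A reader might also object to inflating n for attrition when the original study closed in February 2016. Dividing by 1 − q is the usual conversion and can be compared with the number of families available. It does not change the conclusion.

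**Conclusion.** The point holds as a mismatch between formula and design, together with a missing label. The list gives shared-control-group sizes for a 2:1 many-to-one layout. For the randomised 1:1 comparisons, neither the two-arm-total nor the per-arm reading gives 80% power: about 68% or 93% at d = 0.3, against a need of about 176 per arm. At the fixed cohort size after 15% attrition, the randomised comparisons detect about 0.32 SD (SCH-TPOAb−) and 0.53 SD (TPOAb+).

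These figures assume a two-sided 5% test of each comparison on its own, equal proportional loss in all groups, the Table 2 sizes as the starting point, and the normal approximation. They include no allowance for the five primary outcomes, because the document sets p < 0.05 and contains no adjustment rule.

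**What to change.** In the power section, replace the list with the detectable difference for each comparison at the fixed cohort size after 15% attrition, at two-sided 5% and 80% power. Label every n as per group or total.

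- SCH-TPOAb−, 156 vs 156: about 0.32 SD.
- TPOAb+, 55 vs 56: about 0.53 SD, with power about 35% at d = 0.3 stated alongside.
- Euthyroid comparison, calculated separately and marked as non-randomised: about 0.24 SD for 874 vs 156 and about 0.39 SD for 874 vs 55.

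If the printed formula is kept anywhere, its last denominator should be corrected to the product that reproduces the stated figures. If the sponsor chooses to adjust for the five primary outcomes, figures at alpha 0.01 (0.05/5) may be added, marked as an assumption: about 0.39 SD and 0.65 SD for the two randomised comparisons.

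The cost is a rewritten paragraph and a less favourable stated sensitivity, above all for TPOAb+. No extra patients are needed.
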